### Safety events

#### Definitions

An adverse event (AE) will be defined as any untoward or unfavorable medical occurrence associated with the subject’s participation in SCARLET, whether or not considered related to the subject’s participation in the trial (modified from the definition of AEs in the 1996 International Conference on Harmonization E‐6 Guidelines for Good Clinical Practice). For this study, an AE will include any untoward or unfavorable medical occurrence associated with (1) The Study therapy regimen (any AE occurring after initial dosing of study drug until hospital discharge or study day 29 whichever is longer); or (2) Study-mandated procedures (any AE associated within 12 h of study-mandated phlebotomy).

Severity of AEs experienced by the study subjects will be graded according to the criteria set forth in the National Cancer Institute’s Common Terminology Criteria for Adverse Events (CTCAE) version 5.0. This manual provides a common language to describe levels of severity, to analyze and interpret data, and to articulate the clinical significance of all AEs. AEs will be graded Mild (Grade 1), Moderate (Grade 2), Severe but not immediately life threatening (Grade 3), or Severe with life‐threatening consequences requiring urgent intervention (Grade 4). An AE-related death is considered Grade 5. For grading an abnormal value or result of a clinical or laboratory evaluation, a treatment‐emergent AE is defined as an increase in grade from baseline or from the last post‐baseline value that does not meet grading criteria. Changes in grade from screening to baseline will also be recorded as AEs but are not treatment‐emergent. An abnormal result would also be considered an AE if changes in therapy or monitoring are implemented as a result of the event/result.

A suspected adverse reaction (SAR) will be defined as any AE for which there is a reasonable possibility that the investigational drug caused the AE. For the purposes of safety reporting, “reasonable possibility” means there is evidence to suggest a causal relationship between the drug and the AE. A suspected adverse reaction implies a lesser degree of certainty about causality than adverse reaction, which means any AE caused by a drug (21 CFR 312.32(a)).

An AE or serious adverse reaction (SAR) will be considered “unexpected” if it is not listed in the package insert. An AE or SAR is considered “serious” if, in the view of either the PI or DMSB, it results in any of the following outcomes (21 CFR 312.32(a)): (1) Death; (2) A life‐threatening event (an AE or SAR is considered “life‐threatening” if, in the view of the Investigator, the Medical Monitor, or the DMSB, its occurrence places the subject at immediate risk of death; it does not include an AE or SAR that, had it occurred in a more severe form, might have caused death); (3) Prolongation of existing hospitalization; (4) Persistent or significant incapacity or substantial disruption of the ability to conduct normal life functions; (5) A congenital anomaly or birth defect; or (6) Any other important medical events that may not result in death, be life threatening, or require hospitalization but may be considered serious when, based upon appropriate medical judgment, they may jeopardize the subject and may require medical or surgical intervention to prevent one of the outcomes listed above.

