**Fig. 2 Fig2:**
[figure not shown]
Individual patient schedule. Patients will receive test agent (citicoline or saline placebo) every 12 h for 5 days. Patients will be monitored out to day 29. ABGs—arterial blood gases; CBC/CHEM—complete blood count and chemistry panel; COOS—COVID Ordinal Outcomes Scale; CXR—chest X-ray; S:F—S_a_O_2_:F_i_O_2_ ratio; SOFA—Sequential Organ Failure Assessment

Day 0–1:Informed consent will be obtained.Order for study drug will be placed by the investigator.Initial clinical data will be obtained by research staff using the EMR and recorded in the REDCap study database. Missing laboratory data will be ordered by the investigator.Blood will be drawn from all patients prior to the first treatment dose for laboratory studies.Study drug will be administered i.v. by the bedside nurse operating within their usual scope of practice. The timing of study drug administration may be adjusted up to 4 h on subsequent dosing to achieve standard dosing times.Clinical information, including other drugs administered, will be recorded by the research team into the REDCap study database.

Days 1–5:The patient will be assessed daily by study team for evidence of adverse drug reactions.Dosing with the test agent will continue every 12 h until each subject has received 10 doses total.Laboratory samples will be collected according to the study timeline.Clinical information, including other drugs administered, will be recorded by the research team into the REDCap study database.

Days 6–8:The patient will be assessed daily by study team for evidence of adverse drug reactions or clinical change.Laboratory samples will be collected according to the study timeline.Clinical information, including other drugs administered, will be recorded by the research team into the REDCap study database.

Days 9–29:Patient will be assessed daily by study team for evidence of adverse drug reactions or clinical change.Patients discharged home prior to day 29 will be called on day 29 to verify vital status and discharge location.Patients who withdrew from the trial at any point prior to the cessation of test agent administration

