#### Recording of AEs

AEs will be collected from the time of first dose of study drug, until a subject completes study participation (day 29) or until 30 days after they prematurely withdraw (without withdrawing consent) or is withdrawn from the study. AEs (including SAEs) may be discovered through any of these methods: (1) Observing the subject; (2) Interviewing the subject; or (3) Receiving an unsolicited complaint from the subject. In addition, an abnormal value or result from a clinical or laboratory evaluation can also indicate an AE.

Throughout the study, the PI and his team will record Grade 2 or higher AEs on the appropriate AE/SAE or electronic case report form (eCRF) regardless of the relationship to study therapy regimen or study procedure. Once recorded, an AE will be followed until it resolves with or without sequelae, or until the end of study participation, or until 30 days after the subject prematurely withdraws (without withdrawing consent)/or is withdrawn from the study, whichever occurs first.

The relationship, or attribution, of an AE to the study therapy regimen or study procedure(s) will initially be determined by the PI and recorded on the appropriate AE (AE/SAE or eCRF). Final determination of attribution for safety reporting will be determined by the Medical Monitor, DSMB, PI, and NIAID*.*

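### The seriousness criteria omit new inpatient hospitalization, so a readmission before day 29 is an SAE only if some other item is judged to apply

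*Protocol article*

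**What the plan says.** Under Safety events, Definitions, an event is serious if the PI or the monitoring board considers that it led to one of six numbered outcomes. The third is "3) Prolongation of existing hospitalization". The sixth is a catch-all for other important events "that may not result in death, be life threatening, or require hospitalization but may be considered serious". It applies by medical judgment, where intervention may be needed to avert an outcome listed earlier.

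The same section sets the treatment-related AE window as "any AE occurring after initial dosing of study drug until hospital discharge or study day 29 whichever is longer". Recording of AEs also runs collection to day 29. The Participant timeline expects earlier discharge: "Patients discharged home prior to day 29 will be called on day 29 to verify vital status and discharge location".

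The SAE label is used in four places:
- **Reporting of AEs and SAEs:** the PI reports every SAE within 24 h, whatever its relationship or expectedness.
- **Frequency and plans for auditing trial conduct:** an SAE at least possibly related to treatment triggers an ad hoc DSMB review and a temporary halt in recruitment.
- **Interim safety analysis:** patients with an SAE are counted against Table 2.
- **Outcomes:** a dose is called safe if the SAEs that treating clinicians attribute to it stay below the Table 2 threshold at 20 subjects.

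**The concern.** A discharged patient has no current stay to prolong. A new admission during the remaining follow-up therefore meets no item in the list merely by being an admission. Two assessors could classify the same readmission differently, depending on how each reads item (6). At stake are prompt reporting, the trigger for DSMB review and, for events attributed to citicoline, the count that decides whether a dose is declared safe. The error can only lower the count.

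**Working it through.** **1. The list against its own catch-all.** Item (6) sets aside three kinds of event before it applies. Each should have its own item.

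| Set aside in item (6) | Own item in the list |
|---|---|
| Death | (1) |
| Life-threatening event | (2) |
| Event requiring hospitalization | None; (3) covers prolongation only |

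The inconsistency shows from the document alone and does not depend on the text of the regulation it cites.

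**2. Can the event occur in the window?** Yes. AE collection runs to day 29 even when discharge comes first, and discharge is foreseen even before the 5-day course is complete (Eligibility criteria; Participant timeline). As an example, discharge on day 8 leaves 29 − 8 = 21 days in which a readmission is an AE but not an SAE by item (3).

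**3. Table 2 reproduced.** Inputs from Interim safety analysis: prior Beta(1, 1), acceptable level 0.25, limit 0.85. With r patients with an SAE among n:

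Pr(p > 0.25 | r, n) = upper tail at 0.25 of Beta(1 + r, 1 + n − r) = P(Bin(n + 1, 0.25) ≤ r).

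The smallest r that takes this above 0.85 matches Table 2 for every n from 3 to 20. The article's example of 4 of 9 gives 0.922. The table is not in dispute; only the count compared with it is.

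**4. Effect of one uncounted patient at the boundary.**

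| n | r | Posterior | Above 0.85? |
|---|---|---|---|
| 8 (interim) | 4 | 0.951 | Yes |
| 8 (interim) | 3 | 0.834 | No |
| 20 (final) | 7 | 0.870 | Yes |
| 20 (final) | 6 | 0.744 | No |

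The final-analysis rows are Beta(8, 14) and Beta(7, 15). Moving one patient across the SAE definition reverses the result.

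**5. Why no overall size can be given.** The documents state neither a readmission rate nor an expected rate of attributable SAEs. As an assumption only, let 5% of patients have an attributable readmission as their sole SAE. P(at least 7 of 20) from the exact binomial is then:

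| True attributable rate | All counted | Readmission-only patients missed |
|---|---|---|
| 35% (30% counted) | 0.583 | 0.392 |
| 10% (5% counted) | 0.002 | below 0.0001 |

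The same omission is material near the boundary and negligible far from it. These are illustrations, not estimates.

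**The case against.** A reader might infer that every readmission is lost from the primary safety count, and so apply an all-cause readmission rate to the 7-of-20 boundary. The documents do not support that, for these reasons:

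- **Attribution.** The criterion in Outcomes counts only SAEs attributed to the dose. An unattributed readmission would not count even with a corrected list.
- **Respiratory progression.** Reporting of AEs and SAEs already removes respiratory worsening consistent with known COVID-19 from the SAE category, unless evidence points to citicoline. That is an obvious reason for readmission here.
- **Other items.** Fatal or life-threatening readmissions qualify under (1) and (2), and some others would qualify under (6). The whole list rests on the view of the PI or the board, so judgment alone does not set item (6) apart.
- **Expected rate.** The article reports that serious reactions to citicoline are absent from the literature and that adverse effects are very rare, so a count near 7 of 20 is not what it anticipates.

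A reader might also infer that readmissions go unseen because the call is made "will be called on day 29 to verify vital status and discharge location". That goes too far. The timeline states daily assessment through day 29, Recording of AEs lists interview and unsolicited complaint as sources, Grade 2 or higher AEs are recorded regardless of relationship, and AEs go monthly to the DSMB and Medical Monitor. Call content is operational detail that an article may leave to the full protocol.

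All of this stands as a limit on size. None of it supplies the missing item. Nor does it touch 24 h reporting, which applies regardless of attribution. The interim rule does not repeat the attribution filter in its wording, so the effect there may be wider than at the final verdict.

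**Conclusion.** The list is wrong as written and should be corrected. It omits new inpatient hospitalization, although item (6) presupposes it. A readmission that is not fatal or life-threatening becomes an SAE only through judgment under item (6) or another item. It can therefore miss 24 h reporting, ad hoc DSMB review if related, and the Table 2 counts.

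For the primary safety verdict, the effect is confined to readmissions that are attributed to citicoline, are not set aside as COVID-19 respiratory progression, and occur in a patient with no other counted SAE. Its size cannot be estimated from the documents. What can be shown is that one such patient at the final boundary changes the conclusion for a dose (0.870 against 0.744). This assumes that the final criterion counts patients, as Table 2 does.

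**What to change.** Reword item (3) to cover any inpatient hospitalization, with readmission after discharge named explicitly, alongside prolongation of a current stay. Items (3) and (6) then agree. Table 2 and the posterior rule need no change. The attribution filter and the exclusion for respiratory progression stay as they are. The cost is one phrase in the definition and slightly more SAE reports. A question about readmission in the existing day-29 call is an optional addition.

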#### Recording of AEs

AEs will be collected from the time of first dose of study drug, until a subject completes study participation (day 29) or until 30 days after they prematurely withdraw (without withdrawing consent) or is withdrawn from the study. AEs (including SAEs) may be discovered through any of these methods: (1) Observing the subject; (2) Interviewing the subject; or (3) Receiving an unsolicited complaint from the subject. In addition, an abnormal value or result from a clinical or laboratory evaluation can also indicate an AE.

Throughout the study, the PI and his team will record Grade 2 or higher AEs on the appropriate AE/SAE or electronic case report form (eCRF) regardless of the relationship to study therapy regimen or study procedure. Once recorded, an AE will be followed until it resolves with or without sequelae, or until the end of study participation, or until 30 days after the subject prematurely withdraws (without withdrawing consent)/or is withdrawn from the study, whichever occurs first.

The relationship, or attribution, of an AE to the study therapy regimen or study procedure(s) will initially be determined by the PI and recorded on the appropriate AE (AE/SAE or eCRF). Final determination of attribution for safety reporting will be determined by the Medical Monitor, DSMB, PI, and NIAID*.*

#### Reporting of AEs and SAEs

The PI shall report any suspected adverse reaction that is both serious and unexpected, as described below. The PI shall report an AE as a suspected adverse reaction only if there is evidence to suggest a causal relationship between the study drug and the AE, such as (1) a single occurrence of an event that is uncommon and known to be strongly associated with drug exposure (e.g., angioedema, hepatic injury, or Stevens‐Johnson Syndrome); (2) one or more occurrences of an event that are not commonly associated with drug exposure, but are otherwise uncommon in the population exposed to the drug (e.g., tendon rupture); (3) an aggregate analysis of specific events observed in a clinical trial (such as known consequences of the underlying disease or condition under investigation or other events that commonly occur in the study population independent of drug therapy) that indicates those events occur more frequently in the drug treatment group than in a concurrent or historical control group.

Worsening respiratory function, including but not limited to need for increased oxygen or mechanical ventilation, occurs commonly in this study population and will not be categorized as an SAE if deemed by treating team to be consistent with progression of known COVID-19, unless there is evidence to suggest a causal relationship to citicoline. These events will be captured in the study database but will not be reported as expedited Safety Reports:

Timely reporting of AEs is required by 21 CFR and ICH E6 guidelines. The PI will report all SAEs regardless of relationship or expectedness within 24 h of discovering the event. Other AEs, including expedited reports, will be reported in a timely fashion to the OSU IRB in accordance with applicable regulations and guidelines. The DSMB Annual Study Report to health authorities will include all AEs classified as serious, expected, or suspected. All Safety Reports to the FDA shall be distributed by the DSMB or designee for submission to the OSU IRB.

For SAEs, all requested information on the AE/SAE eCRF will be provided. However, unavailable details of the event will not delay submission of the known information. As additional details become available, the AE/SAE eCRF will be updated and submitted.

The sponsor shall notify the FDA and all participating investigators of Expedited Safety Reports within 15 calendar days; unexpected fatal or immediately life‐threatening suspected adverse reaction(s) shall be reported as soon as possible or within 7 calendar days to appropriate health authorities. The sponsor shall also report any findings from other epidemiological studies, analyses of AEs within the current study or pooled analysis across clinical studies or animal or in vitro testing (e.g., mutagenicity, teratogenicity, carcinogenicity) that suggest a significant risk in humans exposed to the drug that would result in a safety‐related change in the protocol, informed consent, or other aspects of the overall conduct of the study.

#### Interim safety analysis

After enrollment of 8 subjects per group, an interim safety analysis will be performed based on a continuous safety monitoring rule to guide accrual suspension decisions based on unacceptable toxicity and SAEs. The number of patients with an SAE that would warrant temporary suspension of accrual in a given group corresponds to a high posterior probability that the true SAE probability is greater than an acceptable level (i.e., Pr($${p}_{i}$$ > 0.25 | data) > 0.85), where the posterior probability is determined from a Beta-Binomial distribution with Beta (1, 1) as the prior on $${p}_{i}$$. This is illustrated in Table 2.

For example, if 9 patients have been treated and 4 or more patients have an SAE, then accrual will be suspended while data are reviewed more closely and shared with the DSMB so that consensus regarding temporary suspension of accrual, protocol modifications, or decision to close the study early is made. Administration of the blinded study drug may be stopped temporarily or permanently for SAEs attributable to citicoline (in the view of the attending clinician) and in the event of clinical deterioration. In the latter case, the primary treating team is empowered to decide whether to stop the study drug and unblind group assignment. SAEs and unblinding will be recorded and reported to the DSMB at DSMB reviews and interim analyses.

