#### Relevant concomitant care permitted or prohibited during the trial

Enrolled participants will not receive open-label citicoline during the 5-day intervention period. All other treatment decisions will be made by treating clinicians without reference to the protocol. Treatment of the underlying SARS CoV-2 viral infection is left to the discretion of the treating team. Depending on disease severity, and as based on current recommendations from the NIH, treatment may include but is not limited to antiviral therapy with remdesivir and administration of anti-inflammatory agents such as dexamethasone or tocilizumab. Patients deemed high risk for venothromboembolic disease may be treated with either prophylactic or therapeutic anticoagulation as appropriate. Other common medications such as vasopressors, sedative agents, antimicrobials, and neuromuscular blockade will be used in accordance with local standard of care in accordance with best practices.

Serious adverse reactions to citicoline have not been reported in the medical literature and are considered unlikely. Nevertheless, between randomization and day 5, study personnel will review the EMR daily for potential medication interactions with citicoline. There are no rescue medications for citicoline per se; however, reported side effects include headache, nausea, and low blood pressure. Rescue therapies for these side effects include (1) Analgesics for headache (acetaminophen, ibuprofen, rarely narcotics); (2) Antiemetics (ondansetron, metoclopramide); and (3) Fluid bolus for low blood pressure. Should a patient develop evidence of a severe reaction, resuscitation and treatment will be at the discretion of the treating physicians. Specifically, study drug will be discontinued at the time of suspicion of an adverse reaction. If anaphylaxis is suspected, the patient will receive epinephrine, anti‐histamines, and corticosteroids as appropriate. Resuscitation for hypotension will occur with fluids or vasopressor agents.

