### Randomization and blinding

Eligible participants who have provided informed consent will be randomized 1:1:1:1 to 0.5, 2.5, or 5 mg/kg/dose citicoline or placebo. Randomization will be completed in permuted blocks of variable size. Each subject will receive a computer-generated randomization ID number, which will be provided to the research pharmacy, where the appropriate test agent will be prepared. Test agent will be labeled with the ID number and date only.

Patients, treating clinicians, trial personnel, and outcome assessors will be blinded to group assignment until after the database is locked and blinded analysis is completed.

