#### Procedure for unblinding

Unblinding must be approved by the study Medical Monitor ([name]) unless an immediate life-threatening condition has developed, and the Medical Monitor is not accessible. The care team clinician will notify the PI ([name]) and the study statistician of the unblinding event on the next business day. The emergency unblinding will also be reported to the DSMB. A full account of the event will be recorded, including the date and time of the unblinding, the reason for the decision to unblind, and the name of the individual who made the decision and the names of the Medical Monitor and others who were notified. The reasons for unblinding of a participant’s treatment will be included in the final study report.

Any unblinding the study due to an approved interim analysis, final analysis, or study termination will require written approval from NIAID.

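### The interim safety section lets the treating team unblind on undefined clinical deterioration without the Medical Monitor approval required elsewhere, so the blind can be lost selectively before day 3

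*Protocol article*

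**What the plan says.** Four places in the protocol article bear on who may learn the allocation.

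- **Interim safety analysis** allows study drug to be stopped for SAEs attributed to citicoline "and in the event of clinical deterioration. In the latter case", it continues, "the primary treating team is empowered to decide whether to stop the study drug and unblind group assignment". Deterioration is thus a separate trigger from an attributable SAE. It has no definition and no approval step.
- **Procedure for unblinding** states: "Unblinding must be approved by the study Medical Monitor". The single exception is "unless an immediate life-threatening condition has developed, and the Medical Monitor is not accessible".
- **Randomization and blinding** gives the general rule: "Patients, treating clinicians, trial personnel, and outcome assessors will be blinded to group assignment until after the database is locked" and the blinded analysis is done.
- **Reporting of AEs and SAEs** describes how often the trigger may arise: "Worsening respiratory function, including but not limited to need for increased oxygen or mechanical ventilation, occurs commonly in this study population". It gives no rate.

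The primary clinical outcome (Outcomes) is the lowest S:F ratio on study day 3, using the FiO2 in place when SpO2 was lowest. Dosing runs for up to 5 days, so day 3 falls inside the treatment period. The same section judges a dose safe by a count of SAEs that treating clinicians attribute to it.

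**The concern.** Unblinding triggered by deterioration depends on the outcome: the patients most likely to be unblinded are those heading for a low S:F ratio. The people who would learn the arm are also those who can influence what is measured afterwards. The section on concomitant care leaves all treatment other than open-label citicoline to the treating clinicians. Oxygen delivery falls under that, and FiO2 is the denominator of the primary endpoint. Steroids, tocilizumab and ventilation fall under it too.

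The safety outcome is exposed in a second way. Treating clinicians decide attribution for the dose-safety criterion, and the treating team decides whether respiratory worsening is COVID-19 progression and so is not classed as an SAE. A team that knows the arm would make both judgements unblinded.

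The analysis follows intention to treat, so unblinded patients stay in the day-3 comparison. Recruitment is open, so the wording is already in use.

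**Working it through.** The protocol states no figure on this point, so there is none to reproduce. The check is a comparison of the rules, followed by an illustration on assumed inputs.

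**1. Do the two unblinding rules agree?** Take a deteriorating patient and cross two conditions: whether there is an immediate threat to life, and whether the Medical Monitor can be reached.

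| Immediate threat to life | Monitor reachable | Interim safety analysis | Procedure for unblinding |
|---|---|---|---|
| Yes | No | Team may unblind | Team may unblind |
| Yes | Yes | Team may unblind | Approval needed |
| No | No | Team may unblind | Approval needed |
| No | Yes | Team may unblind | Approval needed |

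The rules agree in one case of four. The interim safety section has no cross-reference that would place its permission under the other procedure.

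**2. Can it happen before the endpoint?** Yes. The permission has no time restriction, and the endpoint is on day 3 of a treatment period of up to 5 days.

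**3. How many patients could meet the trigger?** The protocol gives no early deterioration rate. *Assume* 10% to 40% deteriorate by day 3. With 20 per arm (Study design and setting) this is 0.10 × 20 = 2 to 0.40 × 20 = 8 per arm, or 8 to 32 of 80. These are ceilings, because they would require every such patient to be unblinded.

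**4. What could that do to the day-3 comparison?** Suppose a share u of one arm only is unblinded, and their S:F shifts by s standard deviations through changed care. The bias in the arm mean is u × s. With n = 20 × 0.95 = 19 per arm (the protocol's 5% missing-data allowance), a two-sided pairwise t test at 0.05 has 36 degrees of freedom and noncentrality u × s × √(19/2) = u × s × 3.08. The chance of a significant result with no drug effect is then:

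| u (assumed) | s (assumed) | Bias (SD) | Noncentrality | Rejection probability |
|---|---|---|---|---|
| 0.05 | 0.25 | 0.0125 | 0.04 | 0.050 |
| 0.20 | 0.50 | 0.10 | 0.31 | 0.060 |
| 0.20 | 1.00 | 0.20 | 0.62 | 0.092 |
| 0.30 | 1.00 | 0.30 | 0.92 | 0.147 |

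The plan tests each dose against control at 0.05/3 after a global test, so the last column shows sensitivity only. It is not the trial's actual error rate.

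**The case against.** The best reply is that the sections can be read together: the treating team decides to seek unblinding, and the dedicated procedure governs how it is granted. That may be what was intended. The text does not say so, however, and a power to decide is not a power to request. A site acting on the interim safety sentence alone would be following the protocol.

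Safeguards exist. SpO2 is recorded every 2 minutes, unblindings go to the DSMB, and the final report must give reasons. Final attribution for safety reporting rests with the Medical Monitor, DSMB, PI and NIAID. These stand, but recording an unblinding does not undo it, and the dose-safety criterion under Outcomes uses the treating clinicians' view.

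A reader might infer several stronger points that the documents do not support:

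- *The blind fails.* The sentence is a permission, and nothing shows how often it is used.
- *Unblinding is forbidden elsewhere.* It is allowed with approval, or without approval in the stated emergency. The statement that clinicians stay blinded to database lock is a general rule to which such an exception is normal. The real conflict is between the other two sections.
- *Any patient who needs more oxygen may be unblinded.* Deterioration is undefined, so this is the broadest reading rather than the stated rule. The remark that worsening is common was written for SAE classification.
- *Knowing the arm would seldom alter care*, because "There are no rescue medications for citicoline per se". The same section goes on to list side effects and treatments for them, and the point does not need this inference.
- *A specific number of patients or S:F points is at stake.* The only rates in the protocol are mortality figures, which say nothing about deterioration by day 3, and no SD for S:F is given.

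**Conclusion.** The concern holds as a conflict between stated rules. For any deterioration outside the narrow emergency, one section gives the unblinding decision to the treating team and another makes it subject to Medical Monitor approval. Following the first allows unblinding that depends on the patient's course, can come before day 3, and reaches people who influence both primary outcomes.

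The contradiction rests on the text alone and is certain. The harm is possible rather than shown. Its size cannot be computed from the protocol, and the assumed range runs from negligible (0.01 SD) to material (0.30 SD). The illustration assumes that unblinding and the resulting change in care affect one arm only; equal effects in both arms would largely cancel.

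**What to change.** 1. In Interim safety analysis, remove the treating team's stand-alone power to unblind and refer any unblinding to Procedure for unblinding, including its emergency exception. Add to Randomization and blinding that this procedure is the only exception before database lock.
2. Word the decision on study drug and the decision to unblind as separate steps, so that one does not carry the other with it.
3. Report unblindings by arm and by timing relative to day 3 in the final report and, during the trial, to the DSMB in closed session.
4. Reconcile the statements on who may stop study drug and when. Criteria for discontinuing or modifying allocated interventions, the concomitant care section and Interim safety analysis differ; for example, the first does not list deterioration at the treating team's decision. Which clinical rule is right is for the investigators and the DSMB.

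The cost is an amendment of a few sentences and a reminder to site staff. The small downside is that the treating team must contact the Medical Monitor before a non-emergency unblinding, which Procedure for unblinding already requires.
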